**4. OBJECTIVE**

**4.1 PRIMARY OBJECTIVE**

- To determine the effects of probiotics (multistrains of Lactobacillus and Bifidobacterium ) on constipation among Parkinson disease patients compared to placebo
- To determine the effects of probiotics on Gastrointestinal Transit Time (GTT) compared to placebo

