|  | **6. HOSPITAL PROFILE/DEMOGRAPHIC**  **7. STUDY PERIOD**  June 2018 – June 2019  **8. SUBJECTS**  **8.1 TARGET POPULATION**  Patients with Parkinson disease attending the neurology outpatients clinic who fulfil inclusion and exclusion criteria  **9. SAMPLING**  **9.1 INCLUSION CRITERIA**   1. Idiopathic PD diagnosed using UK PD Society Brain Bank Criteria 2. Diagnosis of constipation according to Rome III Functional Constipation Criteria 3. Written informed consent   **ROME III Diagnostic Criteria : Functional Constipation**   \| Functional Constipation \| \| --- \| \| Must include 2 or more of the following:  Straining *  Lumpy or hard stools*  Sensation of incomplete evacuation*  Sensation of anorectal obstruction/blockage*  Manual manoeuvres to facilitate defecation(digital evacuation, support of pelvic floor)*  <3 defecation per week*  ***≥25% of defecations**  Loose stool rarely present without use of laxatives  Insufficient criteria for IBS \|   Based on Longstreth GF et al.Gastroenterology 2006 ;130:1480-1491  **9.2 EXCLUSION CRITERIA**   1. Secondary Parkinsonism 2. Previous history of small and large bowel disease 3. Previous extensive gastrointestinal tract surgery 4. Positive stool occult blood in the last 1 month 5. Use of probiotics or antibiotics in 2 weeks before baseline visit 6. Underlying Dementia 7. Hypothyroidism 8. Diagnosed with major depression and on antidepressant 9. Lactose intolerance   10. Type 1 and Type 2 DM  **10. DATA COLLECTION**  **10.1 METHOD OF DATA COLLECTION**  Patients with idiopathic PD attending the neurology outpatients’ clinic will be invited to participate in the study. All subjects will be screen for constipation by using Rome III Criteria – Constipation Module. Written informed consent will be obtained from all subjects after screening inclusion and exclusion criteria. Baseline demographic data will be recorded into a structured questionnaire.  Screening assessment :  1) Constipation screening using Rome III Criteria – Constipation Module  2) Fecal occult blood testing - negative test will be included in the study  The eligible subjects will be assess on the first visit as below :  1) Constipation symptoms by using Garrigues Constipation module (GQ)  2) Quality of life by using PDQ39 Questionnaire (self-administered malay version )  3) Parkinson Disease severity by using MDS-UPDRS  4)Non motor symptoms of PD by using NMS scale  (All the above questionnaires are validated)  Subsequently, subjects will be instructed to consume 4 red carmine capsule(food colourant) and once the stool turn red in colour, Gatrointestinal Transit Time(GTT) will be measured and recorded. Subjects will then receive a 3g sachet of either probiotics (containing multistrains of lactobacillus and Bifidobacterium 30 Colony Forming Unit) or placebo twice-daily for a duration of 8 weeks. Once consumption completed, subjects need to consume again another 4 red carmine capsule and GTT will be measured and recorded again. Final assessment will be done once subjects completed all the probiotics or placebo given(week 8) and subjects need to be assess again on constipation symptoms, non-motor symptoms, quality of life and disease severity same as done at baseline using the same questionnaire.  **10.2 STUDY PROTOCOL**  Randomization  All patients who fulfill inclusion and exclusion criteria will be stratified based on age, sex and background social economics. Patients who are enrolled will be randomized into two treatment groups which a probiotics group who will receive probiotics (containing multistrains of lactobacillus and Bifidobacterium 30 Colony Forming Unit) or placebo using blocks randomization method, in blocks of 4. Patients and investigator will remain blinded to the treatment protocol.  Following randomization, patients will receive their assigned treatment from the pharmacy department, Hospital Canselor Tuanku Muhriz, PPUKM  Treatment  Active treatment group will receive a 3 gram sachet of probiotics containing multistrains of lactobacillus and Bifidobacterium 30 Colony Forming Unit x 10^9^ to be taken twice daily for 8 weeks.  Composition of probiotics:   \| Lactobacillus acidophilus \| 107mg \| \| --- \| --- \| \| Lactobacillus casei \| 107mg \| \| Lactobacillus lactis \| 107mg \| \| Bifidobacterium bifidum \| 107mg \| \| Bifidobacterium infantis \| 107mg \| \| Bifidobacterium longum \| 107mg \|   Placebo group will receive a 3g sachet of substance (powder form) that has no therapeutic effect to be taken twice daily for 8 weeks.  All test products will be concealed in sealed envelopes, to ensure blindedness  **10.3 STUDY ASSESSMENT**  All patients will be assessed at baseline and week 8 for improvement in constipation symptoms using the Garrigues Constipation Questionnaire^35^, Quality of Life by using self- administered PDQ39 questionnaire (malay version)^36^, disease severity by using MDS-UPDRS and non-motor symptoms by using NMS scale . The Gastrointestinal transit time will be assessed at baseline and week 8 using red carmine capsule. Compliance to treatment, side effects and clinical assessments will be performed by a blinded assessor at baseline and week 8 for both groups.  **Gastrointestinal Transit Time Protocol**  Following randomization, subjects will be instructed to ingest 4 red carmine capsule after last bowel opening. Red carmine capsule is a food colorant and non-toxic to body which is used to measure GTT. The time of ingestion will be recorded. GTT is measured from the time of red carmine capsules consumption and first appearance of red colored stool. The duration from time of ingestion and appearance of red colored stool (Gastrointestinal transit time) will be recorded by patient at baseline, and week 8. The use of laxatives is not forbidden, but patients are required to use as per needed. GTT was measured during pre and end treatment in both groups.  **Constipation-Related Symptom Assessment**  Constipation related symptoms will be assessed using the Garrigues Constipation Questionnaire (GQ)^35^ which is a 21-item that was developed to define the presence of chronic constipation. Only 13 of the 21 items are related to bowel habits. The Rome 111 criteria were used to define constipation. The items are scored using two different four-point Likert scales. The first consisted of ‘never’, ‘sometimes’ (25% of the time) and ‘always’. The second consisted of ‘never’, ‘fewer than once a week’, ‘one or more times a week’ and ‘every day’. Total and cut off scores were not reported.  **Quality Of Life Assessment**  Baseline Quality of life patients will be assess using self-administered PDQ-39^36^ Questionnaire(Malay version) and end of intervention, subject will be assessed again using the same questionnaire. PDQ-39 questionnaire contains 39 items with each item was rated by the patients using one of five categories, from 0 (never) to 4 (always). PDQ-39 summary index (PDQSI) is calculated by dividing the sum of the total raw score by the maximum possible score (156 or 152 points, depending on the patient’s marriage status) and multiplying by 100. In this study, we will use PDQSI as a standardized index for representing PD patients’ life quality.  **Non Motor symptoms (NMS) assessment**  Severity of Non Motor symptoms of each individual will be assess using NMSS Questionnaire. Frequency and severity of each NMS are taken into account. Final total score of disability (0=no disability; 360=maximal disability).  **DDisease severity assessment**  Parkinson Disease severity assessment will be assess using MDS-UPDRS questionnaire. MDS UPDRS has four parts which include nonmotor experiences of daily living (13 items), motor experiences of daily living (13 items), motor examination (18 items), and motor complications (six items). Each subscale now has 0-4 ratings, where 0 = normal, 1 = slight, 2 = mild, 3 = moderate, and 4 = severe.  10.4 **VALIDITY OF TOOLS**  NMS and MDS-UPDRS are public domain questionnaire  Validated score : PDQ 39 (malay version)- permission obtained from author  Garrigues Constipation Questionnaire- awaiting permission from author  **11. STASTICAL ANALYSIS**  Statistical Package for the Social Sciences (SPSS) Software version 2 will be used for statistical analysis. Age, height, weight, body mass index (BMI) and gender were compared between the groups by Student’s t-test and the chi-squared test. General Linear Model will be used to compare intestinal transit time in probiotics and placebo groups before and after 8 weeks of intervention. Pre- and post-probiotics consumption data on clinical evaluation of constipation that will be obtained from all the questionnaires namely Rome III criteria, PDQ-39 Questionnaire and Garrigues Constipation Questionnaire will be analysed using Mc Nemar Test. Independent t-test will be used to compare the differences of intestinal transit time in both groups. Pearson correlation and Simple linear regression analysis will be utilized to explore the relationship and effect between two numerical variables. A p-value <0.05 will be considered as statistically significant.  **11.1 SAMPLE SIZE CALCULATION**  The sample size is being calculated based formula comparing between two proportions. Sample size calculation was performed according to a study by Sakai et al^32^ based on value reported on changes in percentage of bowel movements and complete bowel movements after 3 weeks of probiotics treatment where there was a significant decreased from 73.7% to 36.8%,  Formula for sample size comparing two proportions:  [figure not shown]  Sample size was estimated as follows :  p1 = 0.737  p2 = 0.368  zα = 1.96  zβ = 0.84  n = 0.737 (1 – 0.737) + 0.368 (1 – 0.368 ) X (1.96 + 0.84) ^2^  (0.737 – 0.368) ^2^  n = 0.193831 + 0.232576 X 7.84  0.136161  n = 25 per group  The number of samples per group is further added 20% to compensate for non-response and lost to follow up. The final samples required for each group is 30 patients. |

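### Section 11 names two analyses for the primary transit-time objective without saying which decides, which contrast is tested, or whether baseline transit time is a covariate

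*Combined protocol and SAP*

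**What the plan says.** Section 4.1 lists two primary objectives, and the second is "To determine the effects of probiotics on Gastrointestinal Transit Time (GTT) compared to placebo". Section 10.3 sets the measurement times: "The Gastrointestinal transit time will be assessed at baseline and week 8 using red carmine capsule".

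Section 11 then assigns two between-group methods to this outcome. The first is "General Linear Model will be used to compare intestinal transit time in probiotics and placebo groups before and after 8 weeks of intervention". The second, two sentences later, is "Independent t-test will be used to compare the differences of intestinal transit time in both groups".

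Neither is labelled primary. The text does not say whether the General Linear Model is a repeated-measures model or an ANCOVA, or which of its terms is tested. It does not say whether the differences in the t-test are changes from baseline or the gap between arms at week 8. No covariate is named. All tests share one threshold: "A p-value <0.05 will be considered as statistically significant".

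The sample size in section 11.1 is built on two proportions, so no GTT effect, SD or correlation appears anywhere.

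**The concern.** A primary comparison needs one deciding test that is fixed before the data are seen. Here a reader can derive at least four tests from two sentences: group-by-time in a repeated-measures model, an ANCOVA, a t-test of change, and a t-test at week 8. Some of these coincide and some do not. Where they differ, the plan leaves the analyst free to choose after seeing the results, at a threshold that makes no allowance for the choice.

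The second issue is precision. Baseline GTT is collected in both arms, but nothing commits the analysis to using it as a covariate. With about 25 evaluable patients per arm and no power statement for GTT, an avoidable loss of precision on a primary objective is worth preventing.

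**Working it through.** **Inputs from the documents.** Section 11.1 gives 25 evaluable per arm, 30 after the allowance, and multipliers 1.96 and 0.84. Section 11 gives the 0.05 threshold. Section 10.3 gives GTT at baseline and week 8.

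**Assumptions.** Because the documents give no GTT distribution, I take normal data with equal variances at both times and in both arms, and a baseline to week-8 correlation r of 0.3, 0.5 or 0.7.

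**1. The plan's own figure.** n = [0.737 × 0.263 + 0.368 × 0.632] × 2.8² / 0.369² = (0.193831 + 0.232576) × 7.84 / 0.136161 = 24.55, so 25 per arm; 25 × 1.2 = 30. Both printed figures reproduce. They concern proportions and say nothing about GTT.

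**2. Do the two named tests differ?** With two time points, the group-by-time F in a repeated-measures model equals the square of the change-score t. A numerical check on one simulated data set (25 per arm, true effect 0.5 SD, r = 0.3) gave F = 2.574 and t² = 2.574, both p = 0.115. In the same data the week-8 t-test gave p = 0.023, the ANCOVA p = 0.025 and the group main effect p = 0.115. So on one reading there is a single test, and on others the answers can fall on opposite sides of 0.05. One data set illustrates this; it does not measure how often it happens.

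**3. Cost of choosing.** 40,000 null trials were simulated for each r, with 25 per arm. Each test alone held about 5%. The rejection rate when either of two counts as success:

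| Pair | r = 0.3 | r = 0.5 | r = 0.7 |
|---|---|---|---|
| Change score or week-8 t-test | 8.7% | 9.1% | 9.2% |
| ANCOVA or change score | 7.8% | 7.3% | 6.7% |
| ANCOVA or week-8 t-test | 6.3% | 7.3% | 8.1% |

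**4. Precision.** Relative to a week-8 t-test (variance 1), the change score has variance 2(1 − r) and ANCOVA has 1 − r² in large samples. ANCOVA over change score is therefore (1 − r²) / [2(1 − r)] = (1 + r)/2. The detectable difference at 80% power, in SDs of GTT, is (1.96 + 0.84) × √(2v/25), where v is the relative variance.

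| | r = 0.3 | r = 0.5 | r = 0.7 |
|---|---|---|---|
| v, change score | 1.40 | 1.00 | 0.60 |
| v, ANCOVA | 0.91 | 0.75 | 0.51 |
| ANCOVA / change score | 0.65 | 0.75 | 0.85 |
| ANCOVA / week-8 t-test | 0.91 | 0.75 | 0.51 |
| Detectable, week-8 t-test | 0.79 | 0.79 | 0.79 |
| Detectable, change score | 0.94 | 0.79 | 0.61 |
| Detectable, ANCOVA | 0.76 | 0.69 | 0.57 |

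For an illustrative effect of 0.6 SD, power is 60%/69%/84% with ANCOVA, 43%/56%/78% with change scores, and 56% throughout with week-8 values only. These variances ignore the small cost of estimating the baseline slope (47 rather than 48 residual degrees of freedom, 50 − 3 against 50 − 2).

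**The case against.** The strongest reply is that section 11 is brief rather than wrong. ANCOVA is itself a general linear model, so the proposed analysis may already be what the first sentence means. A change score also uses baseline. A reader might infer that neither named analysis adjusts for baseline GTT, but the documents do not establish this. They show only that no baseline covariate is specified.

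A reader might also infer that the plan necessarily yields two p-values for one question. It does not: on the repeated-measures and change-score reading there is one test. Nor should one presume that a time main effect would be reported as the result, since the objective is against placebo and the t-test is between arms.

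It is tempting to express the gain as 18-54% more patients at no cost (1/0.85 = 1.18; 1/0.65 = 1.54). That needs an assumed r, equal variances and the change-score reading. Against a week-8 t-test the same range of r gives 10-96% (1/0.91 = 1.10; 1/0.51 = 1.96), moving in the opposite direction with r. None of these is a property of this trial.

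Finally, right skew is plausible for a positive duration, but no GTT distribution is given, so a log scale cannot be called necessary.

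All of this stands. It limits the size and certainty of the point. It does not supply the missing choice of test, contrast and covariate.

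**Conclusion.** The point holds as an unresolved choice on a primary objective, with a better single method available from data already planned. On the one reading where the two named tests coincide, there is no inflation of type I error, but the shared test does not condition on baseline. On the other readings, picking the favourable result takes type I error from 5% to roughly 6-9%, given 25 per arm, normal data and r of 0.3-0.7.

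The large-sample variance of ANCOVA is never above that of the change-score test or the week-8 t-test, whatever r is. How far below it lies cannot be found from the documents, so the ratios in the working are a range under stated assumptions. If ANCOVA was intended all along, the change only makes that explicit. The missing power statement for GTT is a separate sample-size matter and is not part of this finding.

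**What to change.** Replace the two GTT sentences in section 11 with one pre-specified primary analysis: an ANCOVA of week-8 GTT on treatment arm with baseline GTT as covariate, reporting the adjusted probiotic-placebo difference with its 95% confidence interval and naming the arm coefficient as the tested contrast. Label the t-test of change from baseline as a sensitivity analysis.

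Two details should be settled in the same text. State whether GTT is analysed in raw units or on a log scale; the log scale is an option because transit time is a positive duration, and it would turn the reported effect into a ratio. State also whether the stratification factors in section 10.2 (age, sex, socioeconomic background) enter the model.

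The cost is SAP wording. No extra patients, visits or measurements are needed, and the software already planned can fit the model.

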A systematic review and meta-analysis of randomized controlled trials in unselected populations of patients with functional constipation demonstrated that the use of probiotics has substantial benefits in stool frequency, transit time and stool consistency with favourable beneficial effects of *B. lactis* strain in particular^31^. The results of this study indicate that, overall, probiotics positively affected all of these measures. Besides, several other cardinal symptoms of constipation also significantly improved for example symptoms such as bloating, sensation of incomplete evacuation, occurrence of hard stools, and ease of stool expulsion.

An open-label, randomized, controlled study by T.Sakai et al^32^ using daily intake of fermented milk for 3 weeks demonstrated that daily consumption of fermented milk containing *Lactobacillus casei strain Shirota (LcS)* significantly reduced the incidence of hard or lumpy stool by 50% in healthy subjects with moderate to severe constipation compared to placebo.

Considering the high prevalence of constipation among PD patients and the positive effects on probiotics alleviating constipation, we attempt to explore the effects of probiotics in PD patients with constipation compared to placebo. We hypothesize that probiotics may be able to partially correct the gut dysbiosis that occurs in PD and improve quality of life among PD patients.

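### The two sample-size rates are described as a before/after change but used as the two arm rates, with no placebo rate justified, so power against placebo is unknown and could be well below the implied 80%

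*Combined protocol and SAP*

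**What the plan says.** Section 11.1 gives the method: "The sample size is being calculated based formula comparing between two proportions". Both proportions come from one cited study, as changes in bowel movements and complete bowel movements "after 3 weeks of probiotics treatment where there was a significant decreased from 73.7% to 36.8" per cent. They are entered as p1 = 0.737 and p2 = 0.368, with zα = 1.96 and zβ = 0.84, giving 25 per group. Power is not stated in words; 80% is what zβ = 0.84 implies. The allowance for losses follows: "The number of samples per group is further added 20% to compensate for non-response and lost to follow up". Then: "The final samples required for each group is 30 patients".

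The first primary objective (section 4.1) is the effect of probiotics "on constipation among Parkinson disease patients compared to placebo", so the comparison of interest is between arms.

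The Literature Review (section 2) describes the same cited study as an open-label, randomised, controlled study of 3 weeks of fermented milk that "significantly reduced the incidence of hard or lumpy stool by 50% in healthy subjects with moderate to severe constipation compared to placebo".

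Section 11 assigns the questionnaire data on constipation, before and after consumption, to a McNemar test. Its general linear model and independent t-test are for transit time. The significance rule is "A p-value <0.05 will be considered as statistically significant". Sections 5.1 and 10.3 allow laxatives as needed in both arms.

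**The concern.** A formula for two independent groups needs the rate expected in each arm at the end of treatment. Section 11.1 describes its two rates as a fall under probiotic treatment. If that is right, 73.7% is a pre-treatment rate standing in for the week-8 placebo rate. The calculation would then assume that placebo patients show no placebo response and no regression to the mean over 8 weeks, although they were selected for having symptoms at entry. No section states or justifies a placebo rate.

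This is the trial's only sample-size justification. If it stays as it is, a null result may be read as coming from a trial with 80% power when the documents do not establish that figure. The calculation is also not tied to a planned test: a paired pre/post McNemar test does not compare the arms.

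**Working it through.** **Inputs.** From section 11.1: p1 = 0.737, p2 = 0.368, zα = 1.96, zβ = 0.84, 25 per group, plus 20%, 30 per group. No week-8 placebo rate is given, so placebo rates below 73.7% are assumptions.

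**Step 1: reproduce the plan's figure.**
n = [p1(1 − p1) + p2(1 − p2)] × (1.96 + 0.84)² / (p1 − p2)²
= (0.193831 + 0.232576) × 7.84 / 0.136161
= 0.426407 × 7.84 / 0.136161 = 24.55, rounded up to 25.
25 × 1.2 = 30. Both figures reproduce.

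**Step 2: link the two descriptions of the source.**
36.8 / 73.7 = 0.50, which matches the 50% reduction in the Literature Review.

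| | Section 11.1 | Literature Review |
|---|---|---|
| Comparison | Fall after 3 weeks of probiotic | Versus placebo |
| Endpoint | Bowel movements and complete bowel movements | Hard or lumpy stool |

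The same figures appear to be described in two incompatible ways.

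**Step 3: power as the placebo rate varies.** The probiotic rate is held at 0.368 and the same unpooled normal formula is used, two-sided 0.05:
power = Φ( (pP − 0.368) / √{[pP(1 − pP) + 0.368 × 0.632] / n} − 1.96 )

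Example, pP = 0.60 and n = 25: variance sum = 0.240 + 0.232576 = 0.472576; standard error = √(0.472576/25) = 0.1375; 0.232/0.1375 = 1.687; Φ(1.687 − 1.96) = 0.39.

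| Week-8 placebo rate | Power, 25 per arm | Power, 30 per arm |
|---|---|---|
| 73.7% (no improvement) | 81% | 87% |
| 70% | 70% | 78% |
| 65% | 55% | 62% |
| 60% | 39% | 46% |
| 55% | 26% | 30% |

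Exact enumeration of the chi-squared test at 25 per arm gives 80, 71, 57, 42 and 29% for the same five rates, so the pattern does not come from the approximation.

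**Step 4: how much placebo improvement can be absorbed.** Solving the same formula for 80% power gives a lowest placebo rate of 73.4% at 25 per arm (73.7 − 73.4 = 0.3 points) and 70.7% at 30 per arm (73.7 − 70.7 = 3.0 points).

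**Step 5: losses.** 30 per arm keeps 25 evaluable up to a loss of 5/30 = 16.7%. A 20% loss leaves 30 × 0.8 = 24, where power is 79% even at a placebo rate of 73.7%.

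**The case against.** The strongest reply is the Literature Review's own sentence. If 73.7% is really the control arm's rate at the end of the cited study, the two-group formula is the right one and the no-placebo-improvement argument falls away. A reader of section 11.1 might infer that the before/after reading is settled. It is not: the documents describe the figures both ways and the source is not available here. What stands is that the two sections conflict and that no placebo rate is justified for this trial. Even on the favourable reading, the rates come from healthy subjects with constipation in an open-label 3-week study, whereas this is a double-blind 8-week trial in Parkinson disease.

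A reader might also blame the permitted lactulose for a loss of power. That does not follow. It is allowed in both arms, and if it lowered both rates equally by 5 to 18.7 points, the same formula at 25 per arm would still give about 80 to 84%. The lower figures in the table need improvement on placebo that is not matched by a further fall on probiotic. Placebo response and regression to the mean remain fair concerns on section 11.1's wording.

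Two smaller replies also have force. The trial enrols 30 per arm, so with no losses there is some slack. And the plan says only that 20% is added, which 25 × 1.2 does correctly. It does not say that a 20% loss is expected, and the shortfall would be one patient per arm.

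**Conclusion.** The point holds in a limited form. The arithmetic is correct; the problem is what the inputs represent. On section 11.1's own wording, the implied 80% power requires essentially no placebo improvement at 25 evaluable per arm, or no more than about 3 points with all 30 evaluable. A placebo rate of 65% would leave 55% (62%) power and 60% would leave 39% (46%), at 25 (30) per arm.

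These figures assume a probiotic rate of 36.8% and hypothetical placebo rates. They do not show that the true power is low, though a reader might take them that way. The supported conclusion is that power is unknown and could be much lower than 80%. The clash between section 11.1 and the Literature Review, over both comparator and endpoint, needs resolving whichever reading is right.

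**What to change.** Keep 60 patients and revise sections 11 and 11.1.

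1. Check the cited study and reconcile section 11.1 with the Literature Review. State which arm and which time point each rate comes from. Do not write either reading into the protocol before checking.
2. State the endpoint that the calculation refers to, which is for the sponsor to confirm, and the assumed week-8 rate in each arm with a justification for the placebo rate.
3. Replace the single power implied by zβ = 0.84 with the range in the table above, with the placebo rates labelled as assumptions.
4. Note that 30 per arm keeps 25 evaluable only up to a 16.7% loss, and that a 20% loss leaves 24.
5. Tie the calculation to a between-arm comparison of the week-8 proportions, reported as a difference with its confidence interval. The paired McNemar test cannot serve this purpose.

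The cost is a check of the source, protocol wording and one added between-arm analysis. It needs no extra patients and no change to treatment. The stated power may look less favourable.
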